## Abstract

**Background:**

A redistribution of tasks between specialized nurses and primary care physicians, i.e., models of advanced nursing practice, has the potential to improve the treatment and care of the growing number of people with dementia (PwD). Especially in rural areas with limited access to primary care physicians and specialists, these models might improve PwD’s quality of life and well-being. However, such care models are not available in Germany in regular healthcare. This study examines the acceptance, safety, efficacy, and health economic efficiency of an advanced nursing practice model for PwD in the primary care setting in Germany.

**Methods:**

InDePendent is a two-arm, multi-center, cluster-randomized controlled intervention study. Inclusion criteria are age ≥70 years, cognitively impaired (DemTect ≤8) or formally diagnosed with dementia, and living in the own home. Patients will be recruited by general practitioners or specialists. Randomization is carried out at the physicians’ level in a ratio of 1:2 (intervention vs. waiting-control group). After study inclusion, all participants will receive a baseline assessment and a follow-up assessment after 6 months. Patients of the intervention group will receive advanced dementia care management for 6 months, carried out by specialized nurses, who will conduct certain tasks, usually carried out by primary care physicians. This includes a standardized assessment of the patients’ unmet needs, the generation and implementation of an individualized care plan to address the patients’ needs in close coordination with the GP. PwD in the waiting-control group will receive routine care for 6 months and subsequently become part of the intervention group. The primary outcome is the number of unmet needs after 6 months measured by the Camberwell Assessment of Need for the Elderly (CANE). The primary analysis after 6 months is carried out using multilevel models and will be based on the intention-to-treat principle. Secondary outcomes are quality of life, caregiver burden, acceptance, and cost-effectiveness. In total, *n*=465 participants are needed to assess significant differences in the number of unmet needs between the intervention and control groups.

**Discussion:**

The study will provide evidence about the acceptance, efficacy, and cost-effectiveness of an innovative interprofessional concept based on advanced nursing care. Results will contribute to the implementation of such models in the German healthcare system. The goal is to improve the current treatment and care situation for PwD and their caregivers and to expand nursing roles.

**Trial registration:**

ClinicalTrials.gov NCT04741932. Registered on 2 February 2021.

## Administrative information

Note: the numbers in curly brackets in this protocol refer to SPIRIT checklist item numbers. The order of the items has been modified to group similar items (see http://www.equator-network.org/reporting-guidelines/spirit-2013-statement-defining-standard-protocol-items-for-clinical-trials/).

## Introduction

### Background and rationale {6a}

With an increase in life expectancy and the associated increase of the number of elderly people, a rise in age-associated illnesses, such as dementia, represents a challenge for health care systems worldwide, where around 50 million people have dementia [1]. This number is expected to double every 20 years to 130 million people living with dementia (PwD) in 2050 worldwide. The increase of PwD will cause an increasing need for care, associated with a substantial increase in cost. Thus, the growing number of PwD is expected to represent a substantial social and economic burden worldwide [1–5]. To decelerate the progression of dementia diseases, PwDs depend on a timely diagnosis and evidence-based post-diagnostic care and support in line with national guidelines [6]. Despite existing evidence for treatments that can improve symptoms and delay the progression of dementia, adherence to national dementia guidelines is currently lacking. As a consequence, the majority of PwD (99%) have at least one, and most have several unmet needs of care [7–9].

Several countries have implemented collaborative care models to overcome the existing challenges of inadequate post-diagnostic support [4, 10–13]. Nurses who work in close cooperation with GPs form the central component of such models. Nurses often have a closer relationship with the patients than GPs, as they usually meet the patients more frequently and are aware about the personal living conditions. Additionally, these nurses have a clearer understanding of person-centered care [14]. In some cases, nurses take on expanded roles including tasks usually performed by GPs. Such concepts of treatment and care are generally summarized as advanced nursing practice (ANP).

Laurent et al. found that delivery of primary healthcare services by nurses instead of physicians, i.e., ANP, results in an equal or possibly better quality of care, including similar or better health outcomes for patients and higher levels of patient satisfaction [15]. Other studies confirmed that ANP- approaches are safe and can optimize treatment and care and patients’ outcomes [13, 16–20]. As a consequence, ANP was implemented years ago in several countries, like Canada, the USA, and most European countries [21]. In most countries, ANP nurses are allowed to order diagnostic tests, to diagnose independently, and to prescribe medications [22–24].

Even though ANP with various degrees of nurse autonomy is common practice [18, 19, 21, 23, 25–32], ANP with independence taking over tasks of GPs does not exist in Germany to date [22]. Within the InDePendent project, dementia care managers (DCM) will take over tasks in cooperation [33]. However, the demand for primary care treatments is expected to rise with the proceeding demographic change. There are already indications of shortages of personal resources in the health care sector. Despite a rising number of GPs over the past decade, the total number of GP hours has decreased and shortages of GPs are imminent, particularly in rural and remote areas. A redistribution of tasks between GPs and nurses provides an option to compensate for this gap [34].

Several initiatives have tried to promote structures for the implementation of ANP models [35–38] in Germany. However, due to the lack of a respective legal framework in German social law, the common practice of ANP in Germany remains theoretical. The only legally possible exception is to implement ANP as part of interventional research to evaluate its safety, effectiveness, and efficiency.

### Objectives {7}

The overall goal of the intervention is (1) to assess and address patients’ and caregivers’ unmet healthcare needs to (2) improve the health and living situation of the PwD and caregivers by providing individualized, person-centered and advanced dementia care management (DCM). In addition, the InDePendent study will examine the acceptance, safety, efficacy, and efficiency of an ANP model in primary dementia care in Germany. The aim of this study is to evaluate, whether dementia-specific qualified nurses and a redistribution of tasks between nurses and primary care physicians could significantly reduce the number of unmet needs of PwD compared to routine care after 6 months. Additionally, the study aims to improve PwDs’ quality of life and relieve the informal caregiver burden. Finally, the aim is to evaluate the acceptance and cost-effectiveness of the intervention.

### Trial design {8}

The InDePendent study is a multi-center, cluster-randomized, controlled intervention study with two arms: (1) patients in the intervention group will receive a model of advanced dementia care management for 6 months, and (2) a waiting-control group, which will start with the usual care for 6 months and subsequently receive the advanced dementia care management (1:2). The flow chart of the study is illustrated in Fig. 1.

**Fig. 1 Fig1:**
[figure not shown]
Flowchart of the InDePendent study

## Methods: participants, interventions, and outcomes

### Study setting {9}

Study participants are recruited within primary care by GPs and specialists, e.g., neurologists and psychiatrists, who are members of five physician networks in three federal states of Germany (Mecklenburg-Western Pomerania, Brandenburg, and Hesse).

### Eligibility criteria {10}

The study population consists of people who meet the following inclusion criteria: (1) age ≥70 years, (2) DemTect Score ≤ 8 or a formal diagnosis of any with dementia by the treating GP or neurologists/ psychiatrists, (3) living in the community (i.e., at home and not institutionalized), and (4) providing written informed consent to participate in the study.

### Who will take informed consent? {26a}

PwDs and their informal caregiver will be asked for their informed consent (IC) to participate in the study. If patients are unable to provide written IC, their legal representative will be asked to provide written IC on their behalf. The GPs will be responsible to verify the patients’ ability to provide a valid IC.

### Additional consent provisions for collection and use of participant data and biological specimens {26b}

Additionally, patients of the two statutory health insurances which participate in the InDePendent study will be asked for their consent to retrieve their health insurance data.

## Interventions

### Explanation for the choice of comparators {6b}

Participants in the waiting-control group will receive care as usual in a primary care setting for 6 months. This group will serve as the comparator for the intervention. After 6 months, the participants in the waiting-control group will change to the intervention group.

### Intervention description {11a}

The DCM concept is based on a collaborative model of care that was previously implemented and evaluated within the DelPHi-MV trial [39]. The InDePendent intervention is extended by advanced nursing roles. Therefore, the intervention will be provided by dementia-specifically-qualified nurses, who will take on particular tasks, that are usually performed by primary care physicians. The DCM qualification was based on curricular guidelines of the Federal Joint Committee on the definition of medical tasks that can be transferred to nurses (§63 Para. 3c of the Social Law Book XI in Germany). The developed curricula were evaluated and approved by the Ministry of Health and the Ministry of Families and were used for the first time to enhance nurses’ competencies to overtake tasks of GP in dementia care. A close cooperation between the GP and the DCM is an important part of the intervention. The intervention is multidimensional and will be individually tailored to the patients’ and caregivers’ specific healthcare needs and their social contexts and resources.

In detail, the intervention consists of four main parts: (1) assessment of patients and caregivers’ unmet medical, pharmaceutical, psychosocial, social, and nursing care needs; (2) development of a plan for needs-based activities; (3) implementation of the intervention tasks needed to address unmet needs; and (4) monitoring of the intervention. The intervention is based on the three principles: (i) management of treatment and care, (ii) medication management, and (iii) caregiver support.

The intervention will be facilitated by a developed computerized intervention management system (IMS) to support the nurses in identifying patients’ and caregivers’ unmet needs and in the development and monitoring of the intervention care plan. The rule-based expert decision support system uses predefined algorithms based on special items within questionnaires and automatically identifies unmet needs and subsequently suggests the corresponding specific treatment and care options to address the identified unmet needs. Therefore, individual patient characteristics were matched to a computerized knowledge base. The IMS system was previously used within the dementia care management of the DelpHi-MV trial, providing evidence that IMS improves the systematic identification of unmet needs and the subsequent recommendation of interventions to address these needs [40].

Therefore, the collaborative model of care (multi-component intervention) will be delivered according to a detailed protocol. The specialized nurse will meet the PwD and their caregiver at their homes for the comprehensive assessment. During the first month of the 6 months intervention, the digitally developed detailed and individual intervention plan will be discussed between the specialized nurse and the GP or specialists, to determine which tasks will be carried out by the specialized nurse and by the physician, respectively.

There are three types of tasks to be carried out by the specialized nurse: (a) interventions after consultation with the GP or specialist (delegation), (b) interventions without prior GP-consultation provided autonomously by the specialized nurse (substitution), and (c) recommendations by the specialized nurse that have to be carried out by the GP or specialist (cooperation).

In addition to the mandatory contact between the nurses and GPs in the first month of intervention, additional contacts after three months are optional, depending on the specialized nurses’ or practitioners’ individual needs and preferences. At the end of the intervention after 6 months, the practitioners receive a comprehensive GP letter with information on the health situation of the patient and recommendations for further management.

### Criteria for discontinuing or modifying allocated interventions {11b}

The intervention will be implemented individually according to patients’ and caregivers’ unmet needs. However, the intervention will be discontinued or modified if:
The patient moves to a nursing homeThe patient diesThe patient revokes his or her consent to participate in the study

### Strategies to improve adherence to interventions {11c}

The specialized nurses take care of the PwDs and their individual needs and will handle all interventions and monitor the completion or incompletion of all tasks frequently. To improve the adherence, the specialized nurses are continuously in and close contact with the PwD during the intervention.

### Relevant concomitant care permitted or prohibited during the trial {11d}

The InDePendent study is a pragmatic trial, which aims to implement DCM with extended nursing roles under routine care conditions. Concomitant care is permitted during the trial and will be documented as accurately as possible.

### Provisions for post-trial care {30}

Not applicable

### Outcomes {12}

The primary outcome of the study is the number of unmet needs in the intervention group compared to the waiting-control group 6 months after baseline. Unmet needs will be assessed with the German version of the Camberwell Assessment of Need for the Elderly (CANE). CANE is available in two versions: one for the PwD (if there is no participating caregiver) and one for the informal caregiver (if the caregiver participates in the study). The result of the CANE is a sum of open and unmet needs.

Secondary outcomes include:
Quality of life

The Quality of Life in Alzheimer’s Disease (Qol-AD) will be used to assess participants’ and caregivers’ quality of life [41]. The German version of the Qol-AD is a well-validated instrument for assessing HRQoL in patients suffering from different dementia diseases, especially for those being mild to moderately cognitively impaired [42].
2.Caregiver burden

Caregiver burden will be assessed by using the Zarit Burden Inventory [43].
3.Acceptance of the care model (process evaluation—only in the intervention group)

In addition to the quantitative analyses, we will perform semi-structured, qualitative interviews evaluated by application of qualitative content analysis [44].
4.Overall health status and economic analyses

For the health economic evaluation, health-related quality of life measured by the EQ-5D-5L and the utilization of healthcare services and informal care measured by the Resource Utilization in Dementia Questionnaire (RUD) [45] and the Questionnaire for Health-Related Resource Use in an Elderly (FIMA) [46] will be assessed.

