### Implementation {16c}

GPs were allocated based on a 1:2 (intervention:waiting list) cluster-level block randomization. The assignment list at the cluster level with defined assignments to the groups was determined prior to physicians’ assignment. The assignment of GPs was implemented when the first patient provided written informed consent in a GP practice. Physicians, therefore, filled in the next available slot on the assignment list, either the waiting list or the intervention group, when the study center received the informed consent documents. Thus, physicians’ participation decisions were made independently and prior to their group assignment.

The allocation sequence will be performed by the evaluation team using RandList software.

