## Assignment of interventions: blinding

### Who will be blinded {17a}

Due to the nature of the intervention in this study, it is not possible to blind the study staff (nurses or practitioners) or the participants. Physicians and patients will become aware of their randomization status throughout the course of the study. The study is not blinded.

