## Data collection and management

### Plans for assessment and collection of outcomes {18a}

After study inclusion, all participants will receive a baseline assessment in their homes carried out by study nurses in the waiting-control group and dementia specialized nurses in the intervention group. Follow-up assessments will be carried out 6 months after the baseline assessment by the dementia specialized nurses in both study groups.

The primary outcome participants’ unmet needs will be assessed by using the Camberwell Assessment of Need for the Elderly (CANE). It consists of 27 categories (including two categories for the caregiver), which assess participants’ needs in various domains (e.g., living situation, household, nutrition, personal hygiene) followed by a question, whether the participant has an unmet need in this area (yes, no) [49]. CANE has been determined suitable for scientific use in dementia and demonstrates appropriate criterion validity [50]. It can easily be used by a wide range of professionals without formal training.

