Secondary outcomes include (i) the Quality of Life in Alzheimer’s Disease (Qol-AD), a 13-item questionnaire designed to provide both a patient and a caregiver report of the quality of life. Each QoL-AD item is rated on a four-point scale, ranging from poor (1) to excellent (4). Results of the Qol-AD can be summarized in a score ranging from 13 to 52, in which higher numbers indicate higher quality of life [51]. (ii) Caregiver burden will be assessed by using the Zarit Burden Inventory, a caregiver self-report 22-item questionnaire. Each item on the interview is a statement which the caregiver is asked to rate using a 5-point scale. Response options range from 0 (never) to 4 (nearly always). The result of the instrument is a sum between 22 and 88, higher results indicate a higher subjective level of burden [43]. (iii) In addition to the quantitative analyses, we will perform qualitative interviews to assess the acceptance and satisfaction of the innovative care concept from different perspectives: people with dementia, caregivers, DCMs, and GPs. Qualitative data will be evaluated using content analyses [44]. (iv) Health economic analyses will assess the cost-effectiveness of the dementia care management compared to usual care by using the EQ-5D-5L [50], RUD (Resource Utilization in Dementia Questionnaire) [45], and FIMA (Questionnaire for Health-Related Resource Use in an Elderly Population) questionnaires [46]. The EQ-5D-5L is a standardized generic instrument for measuring health status. It has been widely used in population health surveys, clinical studies, and economic evaluation, measuring patients’ health utility in five dimensions: mobility, self-care, usual activities, pain/discomfort, and anxiety/depression. Health utilities will be combined with patients’ mortality as quality-adjusted life years by using the area under curve method. The RUD [45] and FIMA [46] instruments will be used to determine the utilization of informal care and caregivers’ productivity losses and the utilization of healthcare services from a payer’s perspective, respectively.

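### The primary CANE count pools patient and caregiver reports with no rule holding the informant constant and no informant term in the model; separately, the Zarit range contradicts its coding

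*Protocol article*

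**What the plan says.** All references are to the protocol article.

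- Outcomes {12} describes two CANE versions: "one for the PwD (if there is no participating caregiver) and one for the informal caregiver (if the caregiver participates in the study"). It then defines a single result: "The result of the CANE is a sum of open and unmet needs".
- Plans for assessment and collection of outcomes {18a} says of the CANE: "It consists of 27 categories (including two categories for the caregiver").
- Eligibility criteria {10} requires no caregiver. After age and cognitive status, the list ends with "3) living in the community (i.e., at home and not institutionalized), and (4) providing written informed consent to participate in the study". Both informant types will therefore occur.
- Implementation {16c}: "The assignment of GPs was implemented when the first patient provided written informed consent in a GP practice". Who will be blinded {17a}: "The study is not blinded".
- Statistical methods {20a} plans a multilevel Poisson regression for the primary outcome, with practice and network as context variables. Further adjustment depends on finding a significant difference between the groups at baseline.
- On the Zarit Burden Inventory, a secondary outcome with 22 items, section {18a} states "Response options range from 0 (never) to 4 (nearly always") and then "The result of the instrument is a sum between 22 and 88".

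**The concern.** A person with dementia and a relative may count that person's unmet needs differently. Under the stated rule, whichever of them answers supplies the primary count, and the two kinds of report are added up as if interchangeable. Because the rule is tied to caregiver participation and not to the baseline visit, a caregiver who drops out would also change the informant within a patient between baseline and 6 months.

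If the mix of informants is the same in both arms, the pooled count is only noisier. If it differs, part of the arm difference in the primary outcome reflects who answered and not how many needs remained. The design leaves a route to imbalance: patients and caregivers who join after their practice is allocated, in a trial where allocation is known. The planned model would not remove the resulting shift unless informant type happened to be picked up by a significance test at baseline. Even then, that would not address switches after baseline.

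**Working it through.** **Inputs from the protocol.** Planned means are 1.87 (control) and 1.22 (intervention), SD 2.0, with five patients per practice (Sample size {14}). The planned difference is 1.87 − 1.22 = 0.65.

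**Who can enter after allocation.** A practice takes its slot at its first patient's consent. With five patients per practice, up to 4 of 5 (80%) can enter afterwards, each with or without a caregiver. The share is lower where several consents reach the study center together.

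**Bias if the mix is unbalanced.** The shift in the arm difference is g × k, where g is the arm difference in the share of caregiver-reported CANEs and k is the mean difference between the two informants for comparable patients. Neither is in the documents, so both are assumed:

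| k (needs) | g = 0 | g = 0.05 | g = 0.10 | g = 0.20 |
|---|---|---|---|---|
| 0.5 | 0 | 0.025 (3.8%) | 0.05 (7.7%) | 0.10 (15.4%) |
| 1.0 | 0 | 0.05 (7.7%) | 0.10 (15.4%) | 0.20 (30.8%) |
| 1.5 | 0 | 0.075 (11.5%) | 0.15 (23.1%) | 0.30 (46.2%) |

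Percentages are of 0.65. The sign of k is unknown, so the shift could inflate or mask an effect.

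**Noise if the mix is balanced.** With a share s of caregiver reports in both arms, pooling adds s(1 − s)k² to the variance, at most 0.25k². For k = 0.5, 1.0 and 1.5 this is 0.0625, 0.25 and 0.5625. Against the planning variance of 2.0² = 4.0 that is 1.6%, 6.3% and 14.1%. A covariate for version removes this component.

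**Possible item-set effect.** The patient categories number 27 − 2 = 25. If the two caregiver categories could count only in the caregiver version, and each were unmet with probability p, the shift would be 2 × p × g. With p from 0.05 to 0.30 and g from 0.05 to 0.20 (both assumed), it runs from 2 × 0.05 × 0.05 = 0.005 to 2 × 0.30 × 0.20 = 0.12 needs, or 0.8% to 18.5% of 0.65. The premise itself is an inference from the text.

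**Zarit range.** The range is the number of items times the lowest code, to the number of items times the highest.

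- As stated, 0–4: 22 × 0 = 0 to 22 × 4 = 88.
- Coded 1–5: 22 × 1 = 22 to 22 × 5 = 110.
- Coded 1–4: 22 × 1 = 22 to 22 × 4 = 88. This matches the printed range but has four points, while the protocol describes a 5-point scale.
- Check on the QoL-AD in the same section: 13 × 1 = 13 to 13 × 4 = 52, which reproduces its stated range.

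The printed maximum of 88 agrees with the stated coding; the minimum of 22 does not.

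**The case against.** The strongest reply has four parts.

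- **Caregiver participation is settled early.** Patients and caregivers are asked for consent to participate (section {26a}). Baseline comes after inclusion, and the individual plan is discussed during the first intervention month. The waiting-control group gets the same intervention after 6 months, so caregivers have less reason to join one arm over the other. This stands against a reading that a reader might infer: that the intervention itself changes who answers, because caregiver support is one of its principles. No section says so, and none describes caregivers joining later. Entry after practice allocation remains a route, and so does a caregiver leaving.
- **The two versions may have the same items.** A reader might infer that patients without a participating caregiver can score on only 25 categories and the others on 27. The protocol never says that the versions differ in content or that the two categories are dropped. A patient may also have a caregiver who does not take part. The inference is plausible but unproven.
- **Some handling exists, and more may be in an analysis plan that is not shown.** The baseline check could pick up informant type, and subgroup analyses by home care situation are planned. But the adjustment rule that the protocol does state is conditional on a significance test, so it makes the covariate set depend on chance and can miss an imbalance large enough to matter.
- **Caregivers' needs are part of the stated goal.** Removing the two caregiver categories from the primary count would redefine the outcome after enrolment began. That is a fair objection, and a sensitivity analysis is enough.

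**Conclusion.** The point holds in a limited form. The protocol pools self-report and proxy report in the primary count, ties the informant to caregiver participation without a rule for keeping it the same at both visits, and names no informant term in the primary model. The consequence is extra noise if the informant mix is balanced and bias only if it is not. The 4–46% range for bias is an illustration from assumed inputs. The documents supply neither the gap nor the informant difference, and no imbalance has been shown.

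The Zarit contradiction is certain but minor, concerns a secondary outcome, and is unrelated to the CANE point. Two stronger readings are not supported. The first is that neither score lies on a valid scale: the Zarit item count, coding and maximum agree, so a 0–4 sum is one scale with a wrong printed minimum. The second is that the electronic case report form would flag valid sums of 0–21: the data management section mentions plausibility checks but gives no limits.

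**What to change.** For the CANE:

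1. State that the informant used at baseline answers again at 6 months where available, and record every switch with its reason.
2. Include baseline CANE version as a prespecified covariate in the primary Poisson model, whatever the baseline comparison shows.
3. Add sensitivity analyses restricted to the 25 patient categories and to patients whose informant did not change. State how the two caregiver categories count when no caregiver participates.

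The cost is one covariate that the trial already has, a few lines of wording, and some missing or switched assessments when a caregiver leaves. The primary outcome keeps its definition. The covariate removes a shift between informants but cannot correct selective entry of patients after allocation. Restricting to unchanged informants selects patients after baseline, so that analysis is supportive only.

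For the Zarit: reconcile the printed range with the stated coding (22 items coded 0–4 give 0–88), and confirm that any limits programmed for data entry agree. This is a wording correction.
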